## Abstract

**Background:**

Violence can have serious short- and long-term impacts on children and young people`s health, development and well-being. On a societal level, it represents a considerable obstacle to economic growth and advancement by lowering human and social capital. Since many children worldwide, especially in low- and middle-income countries, experience violence by teachers at school, there is an urgent need for efficacious and scalable interventions to prevent violence by teachers and improve teacher-student interactions. To this end, the present study examines the effectiveness of the intervention Interaction Competencies with Children – for Teachers (ICC-T) to reduce physical and emotional violence by teachers.

**Methods:**

The study adopts a cluster-randomized controlled trial design with schools (clusters) as level of randomization and three data assessment points: baseline assessment prior to the intervention, the first follow-up assessment 6 months after the intervention and the second follow-up assessment 18 months after the intervention. Across four different sites in Pakistan, a total number of 48 public single-gender high schools (24 girls’ and 24 boys’ schools) are randomly selected. After baseline assessment, half of the schools are randomly allocated to the intervention group, in which teachers at selected schools receive ICC-T, and the other half to the control group, in which teachers receive no intervention. At each school, 30 students in the sixth year of school and all teachers (expected average number: 15) are recruited. Thus, the final sample comprises at least 1300 students and 720 teachers. Data are collected through structured interviews, standardized cognitive tests and school records. Primary outcome measures are student- and teacher-reported physical and emotional violence by teachers in the past week. Secondary outcome measures include teachers’ attitudes towards violence and children’s mental health problems, quality of life and cognitive functioning. Other outcomes are students’ academic performance and peer violence. Data will be analyzed using multilevel analyses.

**Discussion:**

This study aims to provide initial evidence of the effects of ICC-T on children’s exposure to violence at schools, their well-being and functioning in the context of Pakistan.

**Trial registration:**

The clinical trial was registered at ClinicalTrials.gov (ClinicalTrials.gov, 2024) under the identifier NCT06001554 (Preventing Physical and Emotional Violence by Teachers in Public Schools in Pakistan (ICC-T_Pak), 2023) on August 21^st^, 2023.

## Background

Despite global efforts to outlaw violence against children, more than 1.7 billion children – 75% of all children worldwide – experience violence in their upbringing [1]. Strikingly, violence against children in various forms – physical, emotional, sexual or neglect—is most often perpetrated by adults in children’s close social circles, such as parents, caregivers, teachers and other authority figures, who should nurture and protect them [2]. The most common form of such violence is corporal punishment, defined as “any punishment in which physical force is used and intended to cause some degree of pain or discomfort, however light” [3]. Despite being more challenging to conceptualize and operationalize, emotional abuse, which may include spurning, rejecting or denying emotional responsiveness to a child, is a very common form of violence against children as well [4]. According to the World Health Organization, violence against children at the hands of teachers continues to be a serious issue, as 732 million minors aged 6–17 years are estimated to live in countries where corporal punishment in schools is not fully prohibited [5].

The potential negative impacts of childhood violence in schools are manifold and have been documented by numerous studies and reviews, including impairments of brain development, cognitive, emotional, and social functioning, and mental health [6–12]. A review by Gershoff et al. observed consistent links between physical punishment and detrimental outcomes for children across cultural, family and neighborhood contexts [13]. In line with this, Cuartas et al. [9] recently showed that children who were spanked exhibited greater activation in multiple regions of the medial and lateral prefrontal cortex, suggesting that the experience may alter neural responses to environmental threats in a manner similar to more severe forms of violence.

The majority of studies examining the nature and impact of violence against children comes from higher income countries [14] although approximately 90% of the children and adolescents in the world live in low- and middle-income countries (LMICs) [15]. While some evidence suggests that the effects of physical discipline on children’s adjustment may be moderated by the perceived normativeness of the practice in the specific cultural context [16], studies from different LMICs like Colombia, Ghana and South Africa indicate that children usually experience fear and distress in reaction to violence and process violent experiences as threatening [14, 17, 18]. Research shows there are no positive effects of physical punishment whatsoever on improving child behavior or other outcomes for children [13]. On the contrary, evidence suggests that children exposed to corporal punishment, irrespective of the socio-cultural context, are about 24% less likely to be developmentally on track than children who are not exposed to violence [14].

Like in many other LMICs, violence against children is widespread in Pakistan [19]. Corporal punishment of children in home and school settings has become part of a social norm as reflected in a number of survey reports. According to Plan Pakistan and Plan International, majorities of teachers and parents agree that teachers are justified in beating students who are rude or disobedient and that physical punishment is necessary for most children to ensure academic achievement [20, 21]. In line with such attitudes are reports that physical punishment was used in 89% of schools in Punjab, with the practice being most common in public schools, followed by private schools, and then schools for religious education [22]. Similarly, in a large study across 40 public schools in Sindh province, Khuwaja et al. [23] reported that overall 91.4% of boys and 60.9% of girls reported having experienced corporal punishment at school in the previous four weeks, even though the local government had banned corporal punishment in schools in 2011.

With more than 40% of the country’s population under the age of 15 [24], violence by teachers and its detrimental outcomes pose a significant threat to Pakistan’s social capital. Ahmad et al., [25] identified corporal punishment as the main reason for children leaving school at primary level in Pakistan. Given the strong association between exposure to violence and subsequent drug and alcohol use [26–29], violence at school is likely to contribute to the alarming levels of drug abuse observed in Pakistan [30]. As children who are victims of violence are commonly perpetrators of violence against family and community members in later life [31], childhood violence exposure is also likely to be a strong contributory factor to Pakistan’s extremely high prevalence rates of gender-based violence, with 70—90% of married women reporting abuse from their spouses at any time in their lives [32].

One way of enabling social change is through the law, e.g., legally protecting children from abuse with the expectation that legal reform will not only limit the use of these harmful practices but will also change attitudes and thus prevent violence. Socio-legal research from Sweden shows that legal bans on corporal punishment are closely associated with decreases in support and use of corporal punishment and can contribute to a societal change towards a violence free upbringing of children [33, 34]. In Pakistan, corporal punishment of children by teachers and caregivers in institutional settings and workplaces has been legally banned in the federal capital of Islamabad in 2021, but it is still not fully banned in the whole country and not in all settings, including families [35, 36].

While important, legal prohibition alone seems not sufficient to reduce violence against children, as indicated by findings of continuously high prevalence rates of corporal punishment at school in some regions despite existing legal bans [6, 34, 37]. Legal reforms need to be accompanied by programs that address deeply ingrained attitudes and social norms that endorse the use of violence as a necessary practice to raise and educate children. Research suggests that social norms shape beliefs and attitudes towards violent parenting, which in turn guide behaviors [16, 38]. However, this opens the opportunity of preventing violence against children by shifting attitudes and social norms that sustain it [39]. Furthermore, to transform a classroom culture that they themselves grew up with, teachers should be equipped with non-violent interactional skills and competencies as alternatives to violence.

### Evidence-based intervention programs to prevent violence by teachers

To date, there are only few evaluated interventions that have shown to be feasible and efficacious at reducing teachers’ use of violence against children in primary or secondary schools [40, 41]. One of them, the Good School Toolkit, an intervention that aims to shift school operational culture through individual behavior-change techniques, has been implemented and tested in primary schools in Uganda [42]. The IRIE Classroom Toolbox [43], another training program for teachers to support managing child behaviors and foster their social-emotional competence, has been implemented and tested in pre-schools and primary schools in Jamaica. More details on these programs have been discussed elsewhere [40].

The third intervention program in that line is Interaction Competencies with Children – for Teachers (ICC-T), which aims to reduce violence by teachers and improve student–teacher interactions using a week-long workshop format involving teachers. A unique aspect of ICC-T is that it explicitly addresses and seeks to change social norms and attitudes that perpetuate violent practices by encouraging teachers to question them in the light of their own personal experiences of violence. This creates the basis for teachers to be willing to learn, practice and apply alternative non-violent strategies (see more details below in the Methods section). ICC-T has been shown to successfully reduce physical and emotional violence by teachers in cluster-randomized controlled trials (cRCTs) in primary and secondary schools in Tanzania and Uganda [44–46]. In a trial in primary schools in Tanzania, the intervention also led to reduced rates of violence among peers. Currently, ICC-T is being evaluated further in ongoing cRCTs in Ghana, Tanzania, Uganda and Haiti [37, 47].

The present study will implement and evaluate ICC-T in a cRCT in Pakistan, for the first time in Asia and in a predominantly Islamic country. Given the differences between this context and previous implementations of ICC-T, and in line with recommendations for complex interventions [48], we first conducted a feasibility study with two schools in each of the planned four sites in Pakistan. The results of this unpublished study showed a high demand, acceptance and motivation regarding the intervention among participating teachers. Further, ICC-T could be feasibly implemented with few contextual adaptations and the uncontrolled design provided preliminary evidence that ICC-T can effectively reduce teachers’ use of and positive attitudes towards violent discipline in Pakistan. Based on these promising findings and the demonstrated feasibility and efficacy of ICC-T in other contexts, we proceed with testing the effectiveness of ICC-T in Pakistan in a definite cRCT [49]. So far, there have been no scientific effectiveness evaluations of interventions aiming to reduce teachers’ use of violence against children in the context of Pakistan, which underscores the need for this study. The only cRCT of a school violence program conducted in Pakistan, the Right to Play’s school-based intervention aiming to reduce peer violence in public schools, also found a reduction in student-reported corporal punishment by teachers [50]. However, this intervention did not explicitly target violence by teachers by reducing teachers’ positive attitudes towards violence and equipping them with non-violent alternative teaching strategies.

### Objectives and hypotheses

Following a similar approach as previous and ongoing cRCTs of ICC-T [37, 44–47], the present study aims to examine the effects of ICC-T on *a)* teachers’ use of physical and emotional violence against students, and *b)* on students’ functioning (mental health, well-being, and cognitive functioning) in secondary schools in different regions in Pakistan. Based on previous successes of ICC-T, we hypothesize that ICC-T will reduce teachers’ use of physical and emotional violence as reported by teachers themselves and by students in Pakistan schools (*primary outcomes*). Given ICC-T’s focus on changing teachers’ attitudes and the known negative effects of violence on children’s functioning, we also hypothesize that the intervention will reduce teachers’ positive attitudes towards violent discipline and improve students’ functioning as indicated by lower levels of mental health problems and higher levels of quality of life, and cognitive functioning (*secondary outcomes*). Similarly, we hypothesize that ICC-T will improve students’ academic performance and reduce levels of peer violence as reported by students (*other outcomes*).

## Methods

Our protocol adheres to SPIRIT guidelines (*Standard Protocol Items: Recommendations for Interventional Trials*).

### Study design

The study uses a two-arm multi-site cRCT design and is implemented in a total of 48 schools. Half of the schools are randomly allocated to the intervention group, which receives the ICC-T intervention, and the other half of schools to the control group, which receives no intervention. The study involves three data collection phases: baseline assessment directly before the intervention (t0), and two follow-up assessments approximately 6 months (t1) and 18 months (t2) after the intervention. Randomization of schools takes place after baseline assessment. See Fig. 1 for details.

**Fig. 1 Fig1:**
[figure not shown]
Study timeline

#### Study setting and sampling

The study is carried out in four sites in Pakistan: the Islamabad Capital territory and the province of Punjab form one site and the other sites are the two provinces Sindh and Khyber Pakhtunkhwa and the administrative territory of Azad Jammu and Kashmir. These sites were chosen to consider different parts of the country that cover a broad range of geographical, cultural and socio-economic aspects. Within each site, three districts are purposefully selected to represent urban and rural areas. Within Islamabad Capital Territory and the province of Punjab, the three districts are the rural zone of Islamabad and the two Punjabi districts Rawalpindi and Attock. In Sindh, the three districts are Khairpur, Suukur and Naushoru Feroze. In Khyber Pakhtunkhwa, the three districts have been identified but remain to be finally confirmed due to a delayed start of the study activities. In Azad Jammu and Kashmir, the three selected districts are Bagh, Haveli Kahota and Poonch (Rawalkot). When this study protocol was submitted, baseline assessments and ICC-T workshops had already been started in all three districts in Sindh and in two districts in the combined site Islamabad/Punjab.

#### Schools

In each of the selected districts, schools meeting the following criteria are eligible for inclusion into the study. (1) Public, single-gender secondary/junior high schools. With public schooling being the primary model of education and physical punishment most common in public schools, our study is carried out in public secondary/junior high schools. Single-gender schools are selected because majority of the public schools in Pakistan, especially in the rural areas, are single-gender and the teachers are hired accordingly. (2) At least 30 students in the selected class. In case a selected class has fewer than 30 students, it is combined with a neighboring public single-gender school (within 15 km) to a school cluster and 15 students from each school are selected. (3) At least 15 and no more than 50 teachers at a school. In case of fewer than 15 teachers, a school cluster with a neighboring school (within 15 km) is formed and all teachers officially working at these schools are included. The upper limit of 50 teachers is due to practical difficulties related to providing the intervention to a high number of potential participants. (4) The school has not participated in a program aiming to reduce violence by teachers, improve teacher-student relationships and/or children’s wellbeing in the previous three years.

Official lists of available schools are obtained from the relevant authorities and stratified by gender. After listing the gender-stratified schools in each selected district in alphabetical order, two boys’ schools and two girls’ schools are randomly selected, for a total of 12 schools per site (4 schools × 3 districts) and 48 schools in total. One school of the pair of single-gender schools in a district is randomly allocated to the intervention group, while the other school is allocated to the control group. This results in a total of 24 intervention schools and 24 control schools (six intervention schools and six control schools per site). A flow chart depicting the sampling procedures can be found in Fig. 2. All random selections of schools within districts as well as the allocation of schools to the two study conditions are performed by an independent researcher neither belonging to the core research nor the data collection teams using a random number generator.

**Fig. 2 Fig2:**
[figure not shown]
Sampling flow chart

#### Study participants

Due to the longitudinal nature of the study with three data collection points spanning across up to two years, secondary/junior high school students in grade 6 (approximated age: 12–14 years) are included in the study. Students must be below age 18 at the start of the study to be eligible for participation.

#### Sample size

The required sample size was calculated using the software *Optimal Design* [51]. Based on previous trials of ICC-T [37, 47], we expect moderate effects (δ = 0.25) for student-reported violence by teachers and large effects (δ = 0.35) for teacher-reported violence. In previous studies, the intra-class correlation was at 0.1 for teachers and 0.05 for students, and the covariance between baseline and follow-up scores of violence at the school level was around *r* = 0.30 [45, 46, 52]. We expect no drop out at the school level and an estimated attrition rate of 25% for students and 20% for teachers. Together with the specified parameters (α = 0.05; power = 0.80; effect size students: δ = 0.25, effect size teachers: δ = 0.35; ICC students = 0.05, ICC teacher = 0.01; R = 0.30) in total 48 schools with 27 students and 13 teachers per school are required to detect the expected intervention effects. The overall target sample is thus 1300 students and 720 teachers.

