#### Primary outcomes

##### Exposure to violence by teachers

Teachers’ use of physical and emotional violence against students in the past week is assessed using the Teacher–Child Conflict Tactics Scale (CTSTC), an adapted version of the Parent–Child Conflict Tactics Scale (CTSPC; [58]). The CTSTC is answered both by students as victims and by teachers as perpetrators of violence. It includes 16 items on experienced physical violence, seven items on experienced emotional violence and three items on witnessed violence by teachers, which are answered on a 6-point Likert scale from 0 (this has never happened) to 5 (more than 10 times). The items on experienced physical and emotional violence are combined to a total sum score as well as subscale scores. The CTS has been used in previous and ongoing trials of ICC-T and has demonstrated acceptable psychometric properties [37, 44, 45, 47, 52]. The CTSPC has been used in a national survey of violence against children in the home setting in Pakistan [59].

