### Data analyses

Analyses will be conducted using the statistical software *R* [69]. While an extensive evaluation of the psychometric properties of the study measures in the context of Pakistan is beyond the scope of this trial, we will examine internal consistency (through Cronbach’s Alpha) and criterion validity of the study measures (through bivariate correlations between theoretically related concepts) at each timepoint***.*** Baseline data will be used to examine the prevalence of maltreatment in different settings (across all study sites) as well as children’s mental health and well-being. The main analyses focus on testing the effects of the ICC-T intervention on primary (teacher-reported use of emotional and physical violence, student-reported experiences of physical and emotional violence), secondary (teachers’ attitudes towards violence, students’ mental health, well-being and cognitive functioning) and other outcomes (students’ academic performance and experiences of peer violence) at follow-up, with students and teachers as units of analysis. To test the effect of ICC-T over time, we will estimate linear mixed effects models including fixed effects of intervention group (ICC-T, control) and timepoint (baseline, follow-up 1, follow-up 2) and their interactions. Random effects for schools/school clusters and for participants (teachers, students) will account for the nested data structure and individual variability. Participant’ baseline score of the respective outcome and demographics (age and gender) will be included as covariates in the models. Missing data are only expected due to dropout at follow-up and handled through maximum likelihood estimation if the missing data are at least missing at random. This will be assumed if participants completing the follow-up assessments and those who are missing do not differ in primary outcomes and key demographic variables (age and gender) at baseline. Given the higher risk of type I errors associated with multiple outcomes, Holm-Bonferroni correction will be applied to primary outcomes and the false discovery rate (FDR) will be applied to secondary and other outcomes. Results will be presented including appropriate effect sizes and with a measure of precision (95% confidence intervals).

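### The 80% power is computed at an undivided alpha of 0.05, but the primary outcomes are to be tested under Holm; with four outcomes, power per outcome is about 60–61% to 71–73%

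*Protocol article*

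**What the plan says.** **Sample size.** The design parameters are "α = 0.05; power = 0.80; effect size students: δ = 0.25, effect size teachers: δ = 0.35", with one effect size per reporter. Previous studies are cited for the clustering: "the intra-class correlation was at 0.1 for teachers and 0.05 for students". The parameter list in the same paragraph then gives 0.01 for teachers. The school-level correlation between baseline and follow-up is 0.30, and attrition is 25% for students and 20% for teachers. The result is 48 schools with 27 students and 13 teachers per school.

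**Exposure to violence by teachers.** Items on physical and emotional violence "are combined to a total sum score as well as subscale scores".

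**Data analyses.** The outcomes named as primary are physical and emotional violence, each by teacher and by student report. The multiplicity rule is "Holm-Bonferroni correction will be applied to primary outcomes". The model has group, timepoint and their interactions.

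**Study design.** There are "two follow-up assessments approximately 6 months (t1) and 18 months (t2) after the intervention". No section of the article says which follow-up is primary, or whether both belong to the Holm family.

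**The concern.** The power statement and the testing rule do not match. Power is computed as if each reporter had one test at 0.05. The analysis applies Holm to a family that, as listed in Data analyses, has four members. The smallest of four p-values must then pass 0.05/4 = 0.0125 before any other is examined, so a design that just reaches 80% at 0.05 cannot reach 80% per outcome under its own rule.

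The interpretation of a negative result is at stake. A reader who sees one primary outcome fail will take it as the result of an 80%-powered test, which it is not. The family size is also open, because the scale yields a total as well as two subscales per reporter: it could be two, four or six tests. An unseen analysis plan could settle the family, but it would not correct a published power figure computed under a different rule.

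**Working it through.** **Inputs (Sample size section unless noted).** Schools J = 48, split 24/24 (Schools section). Effect δ = 0.25 for students and 0.35 for teachers. Intra-class correlation ρ = 0.05 for students, and 0.1 or 0.01 for teachers. School-level correlation 0.30, so R² = 0.09. Retention 0.75 and 0.80. Two-sided testing is assumed, as sidedness is not stated.

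**Formula.** Two-level cluster-randomized design: λ = Jδ² / (4[ρ(1 − R²) + (1 − ρ)/n]), with power from the noncentral F on 1 and J − 2 = 46 degrees of freedom.

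**Step 1: reproduce the 80%.** After attrition, n = 27 × 0.75 = 20.25 students and 13 × 0.80 = 10.4 teachers.

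- Students: 0.05 × 0.91 + 0.95/20.25 = 0.0455 + 0.0469 = 0.0924; λ = 48 × 0.0625 / (4 × 0.0924) = 8.12; power at 0.05 = **0.796**.
- Teachers, ρ = 0.1: 0.1 × 0.91 + 0.90/10.4 = 0.0910 + 0.0865 = 0.1775; λ = 48 × 0.1225 / (4 × 0.1775) = 8.28; power at 0.05 = **0.804**.
- Teachers, ρ = 0.01: 0.0091 + 0.99/10.4 = 0.1043; λ = 14.09; power at 0.05 = 0.957.

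So 27 and 13 are numbers before attrition, tested at an undivided 0.05, and the teacher value used was almost certainly 0.1. The before-attrition reading also fits the recruitment plan: 27 and 13 completers would need 27/0.75 = 36 students and 13/0.80 = 16.25 teachers per school, more than the planned 30 and 15.

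**Step 2: the same design at the Holm levels.**

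| Case | 0.05 | 0.025 (first of two) | 0.0125 (first of four) |
|---|---|---|---|
| Students, n = 20.25 | 0.796 | 0.702 | 0.600 |
| Teachers, n = 10.4, ρ = 0.1 | 0.804 | 0.711 | 0.611 |
| Teachers, n = 10.4, ρ = 0.01 | 0.957 | 0.921 | 0.870 |
| 30 students recruited, n = 22.5 | 0.817 | 0.727 | 0.628 |
| 15 teachers recruited, n = 12, ρ = 0.1 | 0.830 | 0.743 | 0.647 |
| 27 students as completers | 0.847 | 0.765 | 0.673 |
| 13 teachers as completers, ρ = 0.1 | 0.843 | 0.759 | 0.666 |

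For scale, 80% at 0.0125 with the same cluster sizes would need about 70 schools (students) or 68 (teachers).

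**Step 3: full Holm, simulated with t statistics on 46 degrees of freedom.** The within-reporter correlation is assumed to be 0 to 0.7, with none between reporters; 27 and 13 are before attrition and the teacher correlation is 0.1.

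- Only one student outcome changes: 0.601, essentially the first-step figure.
- All four change: 0.71–0.73 per outcome, 0.38–0.47 for all four, 0.93–0.98 for at least one.
- Family of two (one total per reporter), both change: 0.77 for students and 0.78 for teachers.
- All four change, 30 and 15 recruited: 0.74–0.76 per outcome; family of two, 0.79–0.81.
- All four change, 27 and 13 as completers: 0.77–0.79 per outcome.

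**Step 4: follow-ups, conditional on a rule the article does not state.** Suppose Holm over four outcomes were run separately at each follow-up and success at either counted. With no true effects and independent tests, the familywise error is 1 − 0.9875⁸ = 9.6%. Assuming a correlation of 0.5 between outcomes and 0.5 between follow-ups (0.25 for different outcomes at different follow-ups), simulation gives 8.0%; with all eight tests correlated at 0.5, it gives about 7.5%.

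**The case against.** **The 60–61% figure is a floor.** A reader might infer that the trial's real power is about 60%. The documents do not support that: the Objectives section hypothesizes that physical and emotional violence both fall by both reports, and under that hypothesis Holm gives 71–73%. Power for at least one outcome also stays above 90% under the correlations used here. This objection stands, and both figures should be shown.

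**Four tests is one reading.** One total score per reporter would match the power statement, with its single effect per reporter, and would leave 77–78% against 80%: a small gap. This is a fair reading of the scale's description, but the Data analyses list names physical and emotional violence, and the article does not choose.

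**The printed teacher correlation of 0.01 gives 87% even at 0.0125.** True, but it also gives 95.7% at 0.05, so it cannot be the source of the stated 80%. The student result is unaffected.

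**The planned model also adjusts for each participant's baseline score.** With an assumed individual-level R² of 0.09–0.25 (not in the article), first-step power rises to 0.63–0.68. This narrows the gap without closing it.

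**Follow-ups.** A reader might infer that the two follow-ups go uncorrected. The article does not say so. It is silent, the interaction could be tested jointly, and an unseen analysis plan may name the timepoint. The error rate in Step 4 therefore shows only what one possible rule would cost.

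**Conclusion.** The point holds in this form: the stated 80% is not what the plan's own testing rule delivers per primary outcome. For the four outcomes listed, it is about 60–61% if only one changes and 71–73% if all four do, with 38–47% to win all four. For two totals it is 70–71% at the first step and 77–78% if both change. If 27 and 13 are completers, the first-step figure for four outcomes is about 67%.

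These results assume two-sided tests, R² = 0.09 at school level only, a teacher correlation of 0.1 and the correlations stated in Step 3. The contradiction between 0.1 and 0.01 is an error in its own right and must be reconciled. Holm itself is a valid control, so the defect lies in the power claim and the unfixed family, not in the validity of the tests.

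**What to change.** Before follow-up data are analysed:

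1. Restate the power in Sample size under the Holm rule, giving the first-step figure and the figure when all hypothesized effects hold. Say whether 27 and 13 are before or after attrition.
2. Name the scores that form the primary family: the four subscale scores or the two totals. Whatever is left out becomes secondary.
3. Correct the teacher intra-class correlation so that one value stands throughout the paragraph.
4. As a secondary clarification, name one primary follow-up or include both in the Holm family. The latter makes eight tests if there are four outcomes, with a first step of 0.00625 and first-step power of 0.50–0.51.

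Items 1 to 3 cost a few sentences and a less favourable stated figure, with no extra recruitment. In item 4, naming one follow-up costs a sentence; including both costs power.

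### The teacher intra-class correlation listed for the sample-size calculation (0.01) contradicts the cited evidence (0.1) and cannot produce the stated 13 teachers per school

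*Protocol article*

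**What the plan says.** All the relevant statements are in the Sample size section of the protocol article.

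- Evidence from previous trials: "the intra-class correlation was at 0.1 for teachers and 0.05 for students".
- Inputs listed for the calculation, two sentences later: "ICC students = 0.05, ICC teacher = 0.01", with R = 0.30, "α = 0.05; power = 0.80" and "effect size students: δ = 0.25, effect size teachers: δ = 0.35".
- Baseline adjustment: "the covariance between baseline and follow-up scores of violence at the school level was around *r* = 0.30".
- Attrition: "We expect no drop out at the school level and an estimated attrition rate of 25% for students and 20% for teachers".
- Result: "in total 48 schools with 27 students and 13 teachers per school are required to detect the expected intervention effects".

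The section then gives an overall target of 1300 students and 720 teachers. The Abstract repeats these totals with an expected average of 15 teachers per school, and the Schools section sets a minimum of 15 teachers per school or school cluster.

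**The concern.** One quantity has two values, a factor of ten apart, in the same paragraph. The parameter list is the formal record of what went into the calculation, and teacher-reported violence is a primary outcome. A reader who takes the list at face value cannot reproduce 13 teachers per school and would credit the teacher comparison with far more power than the cited evidence supports. If the calculation had really been run with 0.01, the teacher sample would rest on a much weaker clustering assumption than the previous trials showed. It therefore matters which value was used.

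**Working it through.** **Inputs.** From the Sample size section: J = 48 schools, α = 0.05, power 0.80, δ = 0.35 for teachers and 0.25 for students, r = 0.30, attrition 20% for teachers and 25% for students. From the Schools section: 24 schools per arm. Assumed, because not stated: a two-sided test, R = 0.30 read as a correlation (R² = 0.09), and recruited number = analysed number / (1 − attrition).

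**Formula.** For a two-level cluster-randomised comparison with a school-level covariate and n analysed participants per school, the noncentrality is

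λ = J δ² / (4 [ρ(1 − R²) + (1 − ρ)/n]),

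tested on F(1, J − 2) = F(1, 46). Power of 0.80 needs λ = 8.19. Solving for n:

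n = (1 − ρ) / (B − ρ(1 − R²)), with B = J δ² / (4 × 8.19).

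**Students first, to test the method** (ρ = 0.05). B = 48 × 0.0625 / 32.76 = 0.0916. n = 0.95 / (0.0916 − 0.0455) = 20.6 analysed, and 20.6 / 0.75 = 27.5 recruited, against 27 stated. Power with 27 recruited (20.25 analysed) is 79.6%. The method comes within half a student of the article's figure.

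**Teachers.** B = 48 × 0.1225 / 32.76 = 0.1795.

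- ρ = 0.10: n = 0.90 / (0.1795 − 0.091) = 10.2 analysed; 10.17 / 0.8 = 12.7, so 13. This is the stated figure.
- ρ = 0.01: n = 0.99 / (0.1795 − 0.0091) = 5.8 analysed; 5.81 / 0.8 = 7.3 recruited.

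**How far each result depends on the reading of R** (teachers per school):

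| R² | ρ = 0.01: analysed / recruited | ρ = 0.10: analysed / recruited |
|---|---|---|
| 0 | 5.8 / 7.3 | 11.3 / 14.2 |
| 0.09 | 5.8 / 7.3 | 10.2 / 12.7 |
| 0.30 | 5.7 / 7.2 | 8.2 / 10.3 |

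For ρ = 0.01, even R² = 1 gives 0.99 / 0.1795 = 5.5, so R hardly matters. Other choices do not rescue it. With 23 degrees of freedom (R² = 0) it needs 6.1 analysed, and at 90% power (R² = 0) it needs 8.0 (10.0 recruited). The most extreme variant tried, α = 0.0125 with 23 degrees of freedom and R² = 0, needs 9.5 analysed (11.9 recruited). That α would in turn require 41 to 114 analysed students per school, far from the stated 27.

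**Power for teachers (R² = 0.09).**

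| Recruited per school | Analysed after 20% attrition | ρ = 0.10 | ρ = 0.01 |
|---|---|---|---|
| 13 | 10.4 | 80.4% | 95.7% |
| 15 (720 / 48) | 12 | 83.0% | 97.5% |

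**Totals.** 48 × 27 = 1296, which fits the target of 1300 students. 48 × 13 = 624 and 48 × 15 = 720, so the teacher target corresponds to 15 per school, not 13.

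**The case against.** The strongest reply is that nothing in the trial depends on the misprint. The sample fits the larger, more conservative ICC, that value stands in the same paragraph, and the likeliest explanation is a slip of one decimal place. This stands, and it limits the point to a correction of the record.

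A second reply is that the match between 0.10 and 13 is an inference. It needs R² = 0.09, a two-sided test and 13 to be the number before attrition. The text calls 0.30 a covariance and does not say whether 13 includes attrition. The student check is close but not exact, since 27.5 would round up to 28. This also stands. It weakens the positive identification of 0.10, but not the exclusion of 0.01, which needs none of these readings beyond the stated α, power, δ and number of schools.

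A reader might go further and infer one of three things, none of which the article supports:

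- **That the teacher comparison is underpowered.** It is not: at ICC 0.10 and R² = 0.09 the planned numbers give 80% or slightly more.
- **That 13 is established as the recruited number.** The article never says so, and reading it that way leaves 624 against the 720 target.
- **That a sample-size re-estimation or a later trial would be undersized.** No re-estimation is described, and a later planner would also see the cited 0.1.

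**Conclusion.** The listed teacher ICC of 0.01 is wrong as written. It contradicts the value cited from previous studies, and it calls for about 6 analysed (7 to 8 recruited) teachers per school where the article states 13. An ICC of 0.10 reproduces 13, given R² = 0.09, a two-sided test and 20% attrition already included in that number. The article confirms none of these three, so 0.10 is a strong inference, to be checked against the software input.

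The consequence is a misstated margin on a primary outcome: about 80% to 83% power, depending on whether 13 or 15 teachers per school are recruited, in place of the 96% to 97.5% implied by the list. This is an error in reporting a design input. The design itself is not shown to be deficient.

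**What to change.** 1. Check the teacher ICC entered in Optimal Design and correct the parameter list to 0.10. If the check shows that another value was used, state it with its justification and redo the calculation.
2. State teacher power on the corrected basis: about 80% with 13 recruited per school, or about 83% at 15 recruited and 12 analysed. Say that R = 0.30 enters as a correlation (R² = 0.09), if that is confirmed.
3. Say whether 13 per school is before or after 20% attrition, and reconcile it with the 720-teacher target (624 against 720).

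The cost is one corrected figure and two or three clarifying sentences. If 0.10 is confirmed, neither the number of schools nor the target sample changes.
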